## Abstract

**Introduction:**

Paradoxical intention (PI) is an insomnia treatment developed in the 1970s, which instructs patients to gently attempt to remain awake while in bed at night with the lights off. Previous research indicates PI’s potential in improving insomnia, although no study has been conducted in the last few decades during which the insomnia diagnostic criteria have changed. Additionally, there are knowledge gaps regarding outcomes related to wake after sleep onset, the treatment mechanisms as well as the acceptability and feasibility of the treatment. This study therefore aims to address these gaps by assessing the potential mechanisms, preliminary efficacy, and patient experience and acceptability of PI.

**Methods and analysis:**

We aim to include 40 adult participants with insomnia, aged 18 and above, from the Swedish general population. In this uncontrolled pilot study using a mixed-methods approach, both qualitative and quantitative data will be collected. The trial will be conducted on a self-help online platform, accessible from participants’ homes, with weekly phone call support by therapists. Process and outcome measures will be assessed weekly across a 4-week intervention period and at a 3-month follow-up. A subset of participants will be asked to participate in qualitative semistructured interviews regarding the treatment.

**Ethics and dissemination:**

Ethical approval for this project has been granted by the Swedish Ethical Review Authority (Dnr: 2023-06594-01). All participants will sign informed consent forms on a web service application prior to enrolment. From this mixed-methods study, we anticipate insights into the preliminary efficacy and mechanisms of paradoxical intention for treating insomnia, enriched by patient experience data. Results will be disseminated through peer-reviewed publications. The findings will inform adaptations to the treatment protocol and serve as groundwork for a possible larger scale randomised controlled trial.

**Trial registration number:**

NCT06259682.

STRENGTHS AND LIMITATIONS OF THIS STUDYThe mixed-methods approach of this study strengthens the results by allowing a comprehensive analysis of paradoxical intention’s (PI) efficacy, mechanisms and patient acceptability, informed by qualitative interviews for potential treatment adaptations.The inclusion of patients with both singular and comorbid insomnia enhances the generalisability of findings to a broader population, reflecting real-world clinical settings.The study’s uncontrolled design limits the ability to isolate the effects of PI from non-specific treatment factors.The limited sample size, though typical or even large for a pilot study, may still limit detecting nuanced effects and understanding relationships between process variables.

## Introduction

 Insomnia disorder is characterised by difficulties initiating, returning to or waking up too early from sleep, in combination with daytime consequences (worry or functional impairment). Approximately 10% of the population meets the criteria for insomnia disorder^1^ and the condition is related to several negative effects for those inflicted (eg, psychological distress, decreased quality of life and higher sick leave).^2 3^ Insomnia disorder also tends to remain chronic if untreated^4^ which further highlights the importance of finding and developing effective treatment options for the condition.

During the 1970s, Ascher and Efran^5^ applied paradoxical intention (PI) as an insomnia treatment for patients who had not improved sufficiently after behavioural treatments. PI was described as instructing patients with sleep onset insomnia to try to remain awake for as long as possible rather than to focus on trying to fall asleep as people with sleep issues tend to do. After the first promising study in 1978, other trials in following years also investigated the efficacy of PI with similar results.^6^,^8^ In later years, PI has been reviewed favourably.^9^

Previously, two theoretical models of PI have been presented to account for why PI results in positive effects for patients with insomnia disorder. Originally, PI was based on the understanding that people with insomnia struggle because they believe sleep is a voluntary process and put too much effort into trying to fall asleep.^5^ This effort to sleep was thought to lead to frustration and activate the autonomic nervous system, which makes falling asleep harder. The cycle of self-monitoring, heightened arousal, performance anxiety, sleep effort and failing to fall asleep feeds into itself and creates a vicious cycle. In this view, PI works by reducing performance anxiety around sleep.

In a second model, PI was seen in the light of the attention-intention-effort model (AIE).^10^ This model acknowledges the aspects of anxiety and effort but highlights additional factors. It suggests that people with insomnia pay excessive selective attention to ‘threatening’ sleep-related cues (like a beating heart or external noises), which then leads to a conscious intention to fall asleep. This intention inhibits the normal process of winding down (dearousal), and the heightened intention to sleep leads to both direct (actively trying to sleep) and indirect (extending time in bed) sleep efforts. The AIE model views PI as a way to manipulate this intensified sleep intention by encouraging the individual to remain passively awake or to abandon the direct intention to try to fall asleep.

Additionally, the concept of acceptance, which stems from acceptance and commitment therapy (ACT)^11^ could also be considered a possible mechanism. Indeed, in one study of PI, the instructions given to participants involve ‘giving up trying’^12^ which is similar to instructions seen in later ACT treatments for insomnia.^13^ Some studies have also shown that mindfulness interventions that target psychological flexibility, the theoretical model underlying acceptance and mindfulness interventions, to be effective in treating insomnia disorder.^13 14^ This further gives credence to the idea that acceptance or psychological flexibility is a possible mechanism in insomnia and could be relevant to PI.

Lastly, the concept of metacognition has been increasingly investigated in insomnia during the last decade. Metacognitions have been mentioned in diverse theoretical contexts, which makes synthesis more difficult. For instance, Ong *et al*^15^ developed a metacognitive model of insomnia, which shares mainly connections with other mindfulness and acceptance models. Other researchers have looked at metacognition in the context of the self-regulatory executive function model.^16^ However, these differences withstanding, a core definition of metacognitions might be retained as ‘mental events about one’s thinking’.^17^ Certain studies show that metacognitions regarding insomnia have a mediating role between emotional stability and the effects of self-reported sleep quality.^18^ Even trait neuroticism has been shown to be partially mediated by metacognitive assumptions in the domain of insomnia.^19^ This line of research taken together shows that metacognitive theories are emerging as promising in explaining phenomena within insomnia. PI can be seen as challenging the underlying metacognitions about need for control and danger of unrestrained cognition that may be involved in insomnia disorder.

### Prior evidence of PI for insomnia

The efficacy of PI has been reviewed over the years. The American Academy of Sleep Medicine has twice reviewed PI and concluded that the treatment component is an empirically supported intervention^20^ and categorised PI as a well-established treatment.^21^ Between 2006 and 2018, articles on PI for insomnia are non-existent which reflects its diminishing use in clinical practice. A narrative review on cognitive techniques for insomnia in 2018^22^ showed that PI has empirical support as an insomnia treatment. This was followed by the first comprehensive systematic review and meta-analysis of studies that explore the efficacy of PI for insomnia.^9^ In this review, 10 trials examining PI as a sole intervention were identified. Overall, the beneficial effects for PI were larger when compared with passive rather than active comparators, with the largest being obtained for difficulty falling asleep and the smallest for sleep onset latency. Relative to passive comparators, PI significantly improved sleep onset latency, difficulty falling asleep, number of awakenings, restedness and increased total sleep time with a negligible effect size on sleep efficiency. Compared with active comparators, PI demonstrated moderate improvements in difficulty falling asleep, number of awakenings, and restedness, and negligible effect sizes on sleep onset latency and total sleep time.^9^ A reasonable conclusion from this literature would be to state that PI tentatively has similar efficacy as other cognitive and behavioural interventions for insomnia.

### Limitations of previous research on PI

Quantitative data from three studies in the meta-analysis showed that PI was largely superior to passive comparators on a proposed mechanism of change: sleep performance anxiety. This finding strengthens the notion that decreased performance anxiety is a mechanism through which PI might work. One large concern is that in the three studies’ statistical analyses, the proposed mechanisms-of-change variables are examined as dependent variables; as such, they do not indicate whether changes in psychological processes (eg, performance anxiety) are mechanisms of change in PI outcomes. Performing mediational analyses would further advance the field by clarifying whether insomnia improvements are a result of changes in theorised variables. Also, as the theoretical development regarding insomnia has developed further since these studies were conducted, there are other processes that might explain how PI works, such as acceptance and metacognitions.^23^ With these limitations considered, new studies are needed that examine mechanisms-of-change variables with an appropriate statistical approach and measure all proposed mechanisms of change.

Several other important limitations and uncertainties with the empirical literature on PI were also identified.^9^ Among them were an almost exclusive focus on participants meeting criteria for sleep-onset insomnia or primary insomnia and thereby limiting knowledge of other insomnia groups, such as those with sleep maintenance issues or insomnia comorbid with other psychiatrics conditions which is common in the population.^24^ Also, previous studies largely lack information on how PI was administered (eg, training of therapists) and other important treatment-relevant domains pertaining to patients’ experiences (acceptability, adherence, credibility and expectancy ratings, and perceived usefulness of PI). Additionally, too few trials assessed the long-term efficacy of PI. All these limitations hamper the possibility of drawing strong conclusions about the efficacy of PI.

### Purpose and significance

The most recent meta-analysis supports PI as an effective intervention for insomnia disorder. However, some important aspects of PI have been insufficiently examined, including a modern high-quality assessment of its efficacy, its mechanisms of change and whether patient characteristics predict the treatment effects. The present uncontrolled pilot trial assesses the preliminary efficacy of this treatment on the Insomnia Severity Index (ISI) and secondary outcomes such as quality of life, depression and anxiety. This evaluation serves as groundwork for a possible larger scale randomised controlled trial. It is the first study to examine the effects of PI on insomnia severity using the ISI as well as to comprehensively evaluate secondary outcomes.

While Cognitive Behavioural Therapy for Insomnia (CBT-I) is the preferred first-line treatment for insomnia, there are accessibility issues which prevent many patients from receiving it.^1^ Additionally, research has shown challenges in retaining patients in CBT-I treatments.^25^ In this context, it should be pointed out that PI for insomnia was originally intended for patients who had not improved sufficiently after behavioural interventions for insomnia.^5^ At face value, PI offers a simple, scalable and possibly more acceptable treatment alternative, with a focus on eliminating the behaviours and beliefs that disrupt sleep without demanding greater changes in sleep habits such as sleep restriction. Additionally, there has been a call for increased research into the cognitive aspects of insomnia due to the scarcity of studies in this area.^22^ Consequently, this study could provide practitioners with new methods for the psychological management of insomnia.

This project aims to evaluate PI for insomnia by addressing four key areas: first, the preliminary efficacy of PI on sleep at post-treatment and 3-month follow-up; second, potential mediators of change to identify which processes are altered during PI that may influence treatment outcomes; third, patient characteristics that could moderate the response to PI; fourth, the acceptability and feasibility of PI as perceived by patients. Specifically, the pilot study will assess the immediate and sustained impact of PI on primary (Insomnia Severity Index; ISI) and secondary outcomes, including functional impairment, quality of life, depression, anxiety and sleep diary parameters. Additionally, it will investigate treatment-related aspects such as compliance and adverse events, explore the proposed mechanisms behind PI’s efficacy, determine the influence of patient characteristics on treatment outcomes and capture participants’ perceptions of PI through qualitative interviews.

## Methods and analysis

### Participants and procedures

This planned pilot trial without control condition aims to recruit 40 individuals with insomnia disorder through advertisements in newspapers, clinics and university-related settings across Sweden including campuses and social media. The sample size was determined based on recommendations for single-group pilot studies, which typically suggest 20–25 participants.^26^ Considering potential attrition of approximately 25% during the study period,^27^ and the uncertainty regarding the magnitude of effect sizes of PI for the primary outcome (ISI) and the mediators,^9^ we determined that 40 participants would be appropriate to achieve our aims of assessing the effects, acceptability and feasibility of the trial in preparation for a potential larger scale controlled trial. To be eligible for this trial, participants will undergo three screening phases that consist of first, a questionnaire on the web; second, a telephone interview with a structured assessment of inclusion and exclusion criteria using a standardised format, conducted by clinical psychologists or last year master students in psychology; and finally, the completion of a sleep diary (7 days). The criteria used for inclusion and exclusion in the three screening phases are based on expert recommendations for a standard research assessment of insomnia and the Diagnostic and Statistical Manual of Mental Disorders, Fifth Edition (table 1); noteworthy is that all forms of insomnia will be allowed in the study, including comorbid insomnia, which is more common than insomnia without other comorbid disorders.^1^

**Table 1 T1:** Inclusion and exclusion criteria

Inclusion criteria	Exclusion criteria
Insomnia disorder (according to DSM-5 criteria) with or without psychiatric comorbidity	Severe depressive episode with suicidal intentions or actions
Age over 18Swedish resident and Swedish language proficient	Recent changes in psychopharmacotherapy (within the last 3 months) or use of ‘as-needed’ hypnotic medications during the trial
	Current or past diagnosis of psychotic or bipolar disorderCurrent substance use disorder

DSM-5Diagnostic and Statistical Manual of Mental Disorders, Fifth Edition

Following screening, the individuals offered to be part of the study will be presented with informed consent forms via the internet therapy platform and given the chance to ask questions verbally and in writing before signing. The participants who sign the informed consent form will be given baseline measures including checks for therapy credibility and expectancy and questions about concomitant treatments. Weekly outcome and process measures will follow in combination with treatment and at termination, checks for treatment adherence, treatment compliance and adverse events will take place. Throughout the 4-week treatment, weekly short (15 min or less) meetings with a therapist will take place via phone or videocalls. These meetings have the intention of offering individual support on the use of PI as well as attempting to solve any issues the participant might face with regard to implementing PI correctly.

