Eligibility screening, demographic information and informed consent	Constructed items	x						
Items on previous treatments, participants’ experience and engagement in treatment	Constructed items	x					x	

BBQ, Brunnsviken Brief Quality of life; CEQ, Credibility and Expectancy Questionnaire; CSQ, Client Satisfaction Questionnaire; DASS-21, Depression Anxiety Stress Scale-21; FUfollow-upGSES, Glasgow Sleep Effort Scale; ISI, Insomnia Severity Index; MCQ-I, Metacognitions Questionnaire-Insomnia; NEQNegative Effects QuestionnaireSAS, Sleep Anxiety Scale; Sleep diaryideographic sleep diarySPAQ, Sleep Problem Acceptance Questionnaire; WweekWSAS, Work and Social Adjustment Scale

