#### Mechanisms and predictors

The following mechanisms of change will be measured. Sleep-related performance anxiety (Sleep Anxiety Scale; SAS).^12^ The SAS is an 8-item scale measuring anxiety specifically related to sleep. Items are rated on a 3-point scale with higher scores reflecting greater sleep-related anxiety. Sleep effort will be measured with the Glasgow Sleep Effort Scale,^34^ a 7-item scale assessing the extent of effort exerted to initiate or maintain sleep. Items are rated on a 3-point scale, with higher scores indicating more effort regarding sleep. Sleep Problem Acceptance Questionnaire^35^ is an 8-item scale that evaluates acceptance of sleep difficulties and willingness to engage in life despite them. Items are rated on a 7-point scale with higher scores indicate greater acceptance and less avoidance of sleep issues. Metacognitions Questionnaire-Insomnia Short Version,^36^ a 20-item scale that assesses metacognitions related to sleep and insomnia and its consequences. Items are rated on a 4-point scale; higher scores indicate more dysfunctional metacognitions. To investigate predictors for PI, the following areas will be assessed and screened at pre-treatment: sociodemographics (ie, age, gender, educational attainment, marital status and employment status), insomnia symptoms, use of other sleep treatments (eg, pharmacological), and psychiatric comorbidity and medical comorbidity (assessed using sections of the MINI clinical interview^37^ as well as self-reported prior diagnoses).

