## Discussion

This prospective pilot study also has several strengths. First among these is the mixed-methods approach, which allows for a deeper understanding of the treatment’s feasibility and acceptability, the qualitative interviews are thought in a later stage to be informative of subsequent alterations in the delivery and rationale of the technique which echoes a more recent interest in participatory research and adaptive designs.^45^ Second, the focus on mechanisms and predictors allows us greater precision in formulating why and under which circumstances PI might work. The fact that PI, in essence, only contains a single treatment component also enhances the possibility of claiming specificity of the mechanisms, although ideally, there would be a control condition with another single technique intervention. Third, the wider inclusion of patients with both singular and comorbid insomnia means that results are generalisable to a more representative sample since comorbidity seems to be the norm in most investigated populations.^1^

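### Table 1 screens for recent and as-needed drug treatment but lists no matching criterion on recent or ongoing psychological treatment for insomnia, in a trial whose effect estimate is an uncontrolled pre-post change

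*Protocol article*

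**What the plan says.** The trial has one group: "This planned pilot trial without control condition aims to recruit 40 individuals with insomnia disorder". Participants and procedures presents Table 1 as the criteria for all three screening phases. Its only criterion on other treatment concerns drugs: "Recent changes in psychopharmacotherapy (within the last 3 months) or use of ‘as-needed’ hypnotic medications during the trial". The remaining exclusions cover severe depression with suicidality, psychotic or bipolar disorder, and substance use disorder. Inclusion is broad: "Insomnia disorder (according to DSM-5 criteria) with or without psychiatric comorbidity". Recruitment runs "through advertisements in newspapers, clinics and university-related settings across Sweden including campuses and social media".

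Information on other treatment is collected in three places:

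- Baseline measures include "questions about concomitant treatments" (Participants and procedures).
- Table 2 lists "Items on previous treatments, participants’ experience and engagement in treatment" at inclusion screening and week 4.
- Mechanisms and predictors names "use of other sleep treatments (eg, pharmacological" among the candidate predictors.

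Data analysis estimates the effect of PI from the baseline-to-post change in linear mixed models. Patient characteristics appear there only as exploratory covariates in the mediation analyses. The Discussion recognises that unreported changes in medication could bias the sleep outcomes, and it plans reminders to report them. It says nothing comparable about psychological treatment.

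**The concern.** Without a control arm, little separates the effect of PI from anything else that changes over the same 4 weeks, apart from keeping other treatment stable. The plan accepts this for drugs, and the same reasoning applies to psychological treatment of insomnia. Purpose and significance calls CBT-I the preferred first-line treatment, so it is an obvious candidate for concurrent care.

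Two aims are exposed. The first is preliminary efficacy on the ISI. The second is mediation: an insomnia treatment may also act on sleep effort, sleep anxiety, acceptance or metacognitions, and the mediation model has only the time interval as its X, so any other cause of change over that interval is absorbed. The Discussion argues that PI "only contains a single treatment component also enhances the possibility of claiming specificity of the mechanisms". That argument is weaker for any participant who is receiving a second active treatment. The result also feeds the decision on whether a randomised trial is warranted.

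**Working it through.** **1. Drug and psychological treatment, side by side**

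| | Drug treatment | Psychological treatment for insomnia |
|---|---|---|
| Criterion in Table 1 | Change within 3 months, or as-needed hypnotics, excluded | None listed |
| Recorded before treatment | Yes (screening items, baseline questions, predictor list) | Probably yes, through the same general items |
| Safeguard during the trial | Reminders to report changes (Discussion) | None stated; Table 2 repeats the treatment items at week 4 but not at 3-month follow-up |
| Used in the stated primary ISI analysis | No | No |

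Someone two weeks into CBT-I who still has insomnia disorder is not caught by any listed criterion. Study timeline puts recruitment in autumn and winter 2024 and the start of treatment in spring and summer 2025. Other care could therefore also begin between screening and baseline. The baseline question could reveal it, but no stated rule acts on the answer.

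**2. Form of the bias**

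Let q be the share of participants in a concurrent insomnia treatment and c the extra ISI improvement it brings over the 4 weeks.

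Observed mean change = PI effect + other influences + q × c

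The term q × c does not depend on sample size, so recruiting more participants would not reduce it.

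**3. Illustration**

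The document gives no figure for this bias, so there is none to reproduce. Neither q, c nor the SD of the ISI change is stated; all three are assumptions.

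- Low: 0.05 × 4 = 0.2 points
- Middle: 0.10 × 6 = 0.6 points
- High: 0.20 × 8 = 1.6 points
- Wider grid (q 5-30%, c 2-8): 0.05 × 2 = 0.1 to 0.30 × 8 = 2.4 points

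For scale, the article's target of 40 and attrition of about 25% leave 40 × 0.75 = 30 participants. With an assumed SD of 5 the standard error of the mean change is 5/√30 = 0.91. It would be 5/√40 = 0.79 if all 40 contributed. The middle case is 0.6/0.91 = 0.66 of a standard error. With c = 6, the bias equals one standard error when q = 0.91/6 = 0.15, about 6 of 40 participants.

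**4. Precision cost of leaving affected participants out**

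With 10% affected, 3 of 30 are removed and 27 remain: 5/√27 = 0.96, against 0.91.

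**The case against.** The strongest reply is that this argues from the silence of a condensed table. A reader might infer that the trial knowingly admits people in CBT-I and credits their improvement to PI. The document does not support that. No sentence says such people are eligible, and the full protocol is not shown. Table 1 may also be incomplete: the Discussion mentions an inclusion requirement of stable daily sleep medication that does not appear in those terms in the table. The structured telephone interview could ask about psychotherapy. This limits the point to what is listed, but Table 1 is what the article presents as the rule, and eligibility is a protocol matter.

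The authors also call the results preliminary, name the missing control group as a primary limitation, and qualify the specificity argument by saying that a single-technique control condition would be ideal. These caveats stand. None of them names concurrent psychological treatment, which is a specific and avoidable influence rather than a non-specific factor.

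The data needed to detect the problem are largely planned, and a sensitivity analysis may be in an analysis plan that is not shown. Its absence here is therefore not a fault in itself. Recording does make the problem partly visible, but it does not keep affected participants out of the main estimate.

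Two further inferences go too far. One is that the bias is certainly upward: someone long in treatment who still meets the diagnosis may have stopped improving and add little. The other is that affected participants are common. Clinics are only one of several places for advertisements, and the article itself says that access problems keep many patients from receiving CBT-I.

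Finally, excluding people because of psychotherapy for a comorbid condition would cut into the broad inclusion that the authors count as a strength. That stands, and the fix respects it.

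**Conclusion.** The concern holds in a limited form. As listed, the criteria guard the pre-post comparison against recent or as-needed drug treatment but not against ongoing or newly started psychological treatment for insomnia, and no stated primary analysis makes up for this. Any improvement from such treatment would be included in the ISI change and the mediator changes. The case is clearest for recent starters.

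The size is unknown. The illustrative 0.2-1.6 ISI points rest wholly on assumed shares and effects, and the comparison with a standard error of 0.91 rests on an assumed SD as well. They show only that the bias could range from negligible to larger than the sampling error. The point is worth acting on because the plan already applies the same logic to medication and the repair is cheap.

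**What to change.** - **Eligibility.** Extend the stability criterion in Table 1 to psychological treatment for insomnia that is ongoing or was started within the last 3 months, the window already used for drugs. Keep earlier, completed CBT-I allowed. Apply the criterion in the existing telephone interview, and check it again with the baseline question on concomitant treatments.
- **Comorbid conditions.** Keep participants who are in psychotherapy for a comorbid condition, so that the broad inclusion is preserved. Record that treatment, and any newly started psychological treatment, at week 4 and at the 3-month follow-up.
- **Participants already enrolled.** Repeat the primary ISI change estimate without those in concurrent psychological treatment, and report how many there are.

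The cost is a few candidates lost or deferred, one added item at follow-up and one sensitivity analysis on data that are mostly planned already.
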